### Outcome Measures

#### Data Collection Materials

One primary outcome and several secondary outcomes will be assessed in this trial. A number of data collection materials, including validated and study-specific questionnaires, will be used to assess study outcomes at multiple time points over the 3-month period. These tools will be completed in-person under the supervision of the research assistants during the study visits. Among these are the enrollment survey designed by investigators to collect demographic information and subjects’ technology use information, and the Patient-Health Questionnaire (PHQ-8) [18], which will be used as a screener for depression, a potential confounder in this study. If a subject is assessed to have severe depression on this tool, study staff will note this to the file and report immediately to the principal investigator who will duly notify the subject’s oncologist by phone. Additionally, such subjects will be encouraged to contact their physicians regarding this screen.

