### Recruitment Procedure

Participants for this trial will be drawn from cancer patients receiving care at the DFCI on OAMs. On a weekly basis, the research team will identify patients being started on a new cycle of OAM from chart reviews. After identifying potentially eligible patients, we will ask the managing oncologists to give approval to contact the patient about participating in the study. Thereafter, recruitment letters will be sent to all approved patients. One week after recruitment letters have been mailed, research assistants will attempt to contact subjects by phone to provide further detail regarding the study. If subjects are interested in participating, study staff will schedule an enrollment visit with subjects at the DFCI at the subject’s convenience.

All enrollment procedures, including the informed consent process, completing enrollment surveys, and randomization procedures will be performed by trained research assistants. At the enrollment visit, all participants will be instructed to continue to receive usual medical care from their physicians as usual. They will also receive a Medication Event Monitoring System (MEMS) device, a valid measure of adherence used in many chronic diseases, to monitor medication adherence in this study. The bottle cap has a microprocessor that records all instances and times that the bottle is opened. They will be instructed to open their pill bottles only when they want to take their medications. Only subjects randomized to the intervention arm will download and be able to use the CORA mobile app.

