#### Randomization and Blinding

A computer program will be used to randomize subjects into the intervention or control arm in a ratio of 1:1 using random permutated blocks to optimize balance in each treatment at any given point in time during the study. Treatment assignment will be concealed in sealed envelopes prepared by a third party not directly involved in the study. Due to the nature of the intervention, it is difficult to blind the subjects to the treatment assignment, but it will be concealed from the investigators and the data analyst. In addition, the study investigators will not be directly involved in the day-to-day running of the study. This will be done by trained research assistants and a project manager who will report regularly to the investigators on the progress of the study.

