#### Primary Outcome

The primary outcome measure for this study is medication adherence, defined as the percentage of prescribed doses taken as captured by the MEMS device, which all study participants will receive at enrollment. The MEMS, like other measures of adherence, is not without its drawbacks, but it provides an objective measure of when the pill bottle was opened, which correlates well with the timing of medication self-administration. Currently, there is no gold standard measure of medication adherence, but the MEMS has been used extensively in medication adherence studies [19,20]. Additionally, we will also use a patient self-report tool, the Morisky Medication Adherence Scale (MMAS-8) to measure medication adherence [21]. This is an 8-item self-reported questionnaire used to measure medication adherence. Research has shown that self-reporting of medication adherence captures patient adherence to a reasonably accurate degree. The MMAS has been tested in several different settings and has been shown to demonstrate both concurrent and predictive validity of medication adherence. This survey will be administered in-person by trained research staff at study entry, midpoint, and at the end of the study.

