#### Secondary Outcomes

The following secondary outcomes will be measured at various time points during the study:

Symptom severity: This will be measured by the MD Anderson Symptom Inventory (MDASI), which is a validated and widely used survey in clinical practice and research [22]. It is used to assess multiple symptoms experienced by cancer patients and how the symptoms interfere with daily living. Its 13 core items include the most frequently occurring symptoms seen in various cancer types and treatment modalities. It will be administered in-person at study entry, midpoint, and end of study. However, because the tool also captures some symptoms that may occur and resolve acutely, we will also assess symptoms in between study visits at weeks 3 and 9. These in-between study assessments will be self-administered via REDCap, a secure, Web-based app for data collection customizable for individual research studies. It is free and complies with all Health Insurance Portability and Accountability Act regulations (HIPAA). It was developed by a multi-institutional consortium initiated at Vanderbilt University. Participants will receive the REDCap links in their in email to complete the surveys online.Hospital utilizations: This will be measured at the end of the study by a review of the electronic medical records for emergency department or urgent care clinic visits and in-patient admissions.Quality of life: This will be measured longitudinally by the Functional Assessment of Cancer Therapy-General (FACT-G) questionnaire administered in-person at study entry, midpoint, and end of study [23]. Now in its fourth version, this questionnaire is well validated and has been translated into nearly 50 different languages and has been used extensively worldwide. It has four subscales: Physical Well-Being, Social/Family Well-Being, Emotional Well-Being, and Functional Well-Being.Cancer-related fatigue: This will be assessed by the Functional Assessment of Chronic Illness Therapy - Fatigue Version 4 (FACIT-F) at study entry, midpoint, and end of study [24]. It is a self-administered 13-item questionnaire validated for use in chronic illness and frequently used with cancer patients.Anxiety: The Generalized Anxiety Disorder 7-Item Scale (GAD-7) will be used to assess anxiety [25]. This self-administered 7-item questionnaire is a valid and efficient tool commonly used in both clinical practice and research studies to assess the severity of anxiety.Usability and Satisfaction: This is a study-specific questionnaire designed by the authors to collect usability and satisfaction information.

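### Staff who may know the arm administer the MMAS-8 in person and supervise the other visit questionnaires; patient self-completion would remove an avoidable influence on these secondary measures

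*Protocol article*

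**What the plan says.** All references are to the protocol article.

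- **Recruitment Procedure** gives enrolment to one role: "All enrollment procedures, including the informed consent process, completing enrollment surveys, and randomization procedures will be performed by trained research assistants". It adds: "Only subjects randomized to the intervention arm will download and be able to use the CORA mobile app".
- **Randomization and Blinding** says of the assignment that "it is difficult to blind the subjects to the treatment assignment, but it will be concealed from the investigators and the data analyst". The same section leaves the daily running of the study to research assistants and a project manager.
- **Data Collection Materials** says of the questionnaires: "These tools will be completed in-person under the supervision of the research assistants during the study visits".
- **Primary Outcome** defines adherence by the MEMS device and adds the MMAS-8 as a self-report measure: "This survey will be administered in-person by trained research staff at study entry, midpoint, and at the end of the study".
- **Secondary Outcomes** has the MDASI and FACT-G given in person at entry, midpoint and end. It describes the FACIT-F and GAD-7 as self-administered. For the extra MDASI assessments at weeks 3 and 9 it says: "These in-between study assessments will be self-administered via REDCap".

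**The concern.** Concealment covers the investigators and the analyst, who by the article's own account stand outside daily operations. It does not cover the role that handles randomisation and then meets patients at the visits where they report outcomes.

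The MMAS-8 is the most exposed instrument. A patient is asked about pill-taking, face to face, by research staff who may know whether that patient was given an app meant to improve pill-taking. If prompting, or the wish to give a creditable answer, differs between arms, the MMAS-8 contrast is biased. Its agreement with the MEMS result would then be weaker support than it appears. The in-person MDASI and FACT-G carry the same risk to a lesser degree.

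Patients cannot be blinded here, and the article says so. Influence from staff, by contrast, can largely be avoided.

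**Working it through.** **1. Who knows the arm, and who collects what.**

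| Item | What the article fixes | Staff influence possible? |
|---|---|---|
| Randomisation | Done by research assistants | Source of knowledge of the arm |
| Concealment | Investigators and data analyst only | Research assistants not covered |
| MMAS-8 | Administered in person by research staff, three visits | Yes, most directly |
| MDASI, FACT-G at the three visits | Given in person, under supervision | Yes |
| FACIT-F, GAD-7 | Self-administered, but under the general supervision rule | Limited to supervision |
| MDASI, weeks 3 and 9 | Self-completed on the web | No |
| MEMS adherence (primary) | Electronic record of bottle openings | Not a questionnaire |
| Hospital utilisation | Record review | Not a questionnaire |

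No sentence blinds the research assistants or separates those who allocate from those who assess. Answers given before allocation cannot be affected. Recruitment Procedure lists surveys before randomisation but does not make that order a rule.

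**2. The plan's own sample size.** Inputs from Sample Size Estimation: difference 10, SD 16, two-sided alpha 0.05, power 80%.

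n per arm = 2 × (1.960 + 0.842)² × 16² / 10² = 2 × 7.85 × 2.56 ≈ 40.2, rounded up to 41, or 82 in total. With 20% dropout, 41 / 0.8 = 51.25, rounded up to 52 per arm, or 104. Both stated figures reproduce. They rest on the MEMS outcome, so the change proposed here does not alter them.

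**3. Illustration of scale.** Suppose there is no true effect on a questionnaire score, but reporting in one arm is shifted by b SD relative to the other. With 41 per arm, a two-sided 5% t test (80 degrees of freedom) has noncentrality b × √(41/2) = 4.53 × b.

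| Assumed differential shift b | Noncentrality | Chance of a significant result |
|---|---|---|
| 0 | 0 | 5% |
| 0.1 SD | 0.45 | 7.3% |
| 0.2 SD | 0.91 | 14.6% |
| 0.3 SD | 1.36 | 26.9% |

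The values of b are assumptions; the article gives no basis for choosing among them. Only a shift that differs between arms counts, since staff attend visits in both arms.

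**The case against.** The strongest reply is that supervised completion is an ordinary choice, that the article states the limits of its blinding openly, and that the primary outcome is electronic. The supervision sentence already allows patients to fill in forms themselves, and the FACIT-F and GAD-7 are described that way. A condensed article may also leave the division of staff duties to the full protocol. All of this stands, and it confines the point to a suggestion about secondary measures. It does not remove the point, because in-person administration of the MMAS-8 by research staff is a stated rule and not an omission.

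A reader might infer more than the text supports, in five ways:

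- **That every questionnaire result is compromised.** The MDASI at weeks 3 and 9 has no staff present, and the FACIT-F and GAD-7 are exposed to supervision, not interviewing.
- **That the same individual randomises, sets up the app and later assesses a given patient.** The article names one role for randomising and supervising, but does not say the same person does both. Nor does it say that staff install the app; patients download it.
- **That moving the MDASI between in-person and web completion biases the planned analysis.** Both arms follow the same schedule, so a mode effect common to both cancels in the comparison between arms. Entry, midpoint and end share one mode. The Statistical Analysis section does not say that weeks 3 and 9 enter the repeated-measures analysis of variance.
- **That 7%, 15% and 27% measure what the fix would gain.** They do not separate staff influence from patients' own reporting bias, which self-completion would leave in place.
- **That web forms already exist for all instruments.** REDCap is described only for the MDASI at weeks 3 and 9.

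**Conclusion.** The point holds in a limited form. Research assistants randomise, are not among those from whom allocation is concealed, and supervise the visit questionnaires; research staff administer the MMAS-8 in person. Staff who may know the arm can therefore influence the MMAS-8 most, and the MDASI and FACT-G at the visits to a lesser degree. That they do know the arm is an inference from their part in randomisation, and a sound one unless the full protocol separates the roles.

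The size of any bias is unknown, and the error rates above only show how sensitive a comparison with 41 per arm would be to an assumed differential shift. The primary outcome and the sample size are untouched. This is a worthwhile low-priority improvement.

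**What to change.** Amend the Primary Outcome and Secondary Outcomes sections so that patients complete the MMAS-8, MDASI and FACT-G themselves at entry, midpoint and end, as is already described for the FACIT-F and GAD-7. Use paper, or REDCap forms added to the existing MDASI form. Limit the research assistant to checking that forms are complete, without reading items aloud or discussing answers. State as a rule that baseline forms are finished before the allocation envelope is opened.

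The cost is a few extra forms, plus help for some patients if a device is used. No extra staff are needed, and a research assistant at the visit still protects completeness. When the results are reported, patients' knowledge of their own arm should still be named as a limitation of every self-reported outcome.

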#### Primary Outcome

The primary outcome measure for this study is medication adherence, defined as the percentage of prescribed doses taken as captured by the MEMS device, which all study participants will receive at enrollment. The MEMS, like other measures of adherence, is not without its drawbacks, but it provides an objective measure of when the pill bottle was opened, which correlates well with the timing of medication self-administration. Currently, there is no gold standard measure of medication adherence, but the MEMS has been used extensively in medication adherence studies [19,20]. Additionally, we will also use a patient self-report tool, the Morisky Medication Adherence Scale (MMAS-8) to measure medication adherence [21]. This is an 8-item self-reported questionnaire used to measure medication adherence. Research has shown that self-reporting of medication adherence captures patient adherence to a reasonably accurate degree. The MMAS has been tested in several different settings and has been shown to demonstrate both concurrent and predictive validity of medication adherence. This survey will be administered in-person by trained research staff at study entry, midpoint, and at the end of the study.

#### Secondary Outcomes

The following secondary outcomes will be measured at various time points during the study:

Symptom severity: This will be measured by the MD Anderson Symptom Inventory (MDASI), which is a validated and widely used survey in clinical practice and research [22]. It is used to assess multiple symptoms experienced by cancer patients and how the symptoms interfere with daily living. Its 13 core items include the most frequently occurring symptoms seen in various cancer types and treatment modalities. It will be administered in-person at study entry, midpoint, and end of study. However, because the tool also captures some symptoms that may occur and resolve acutely, we will also assess symptoms in between study visits at weeks 3 and 9. These in-between study assessments will be self-administered via REDCap, a secure, Web-based app for data collection customizable for individual research studies. It is free and complies with all Health Insurance Portability and Accountability Act regulations (HIPAA). It was developed by a multi-institutional consortium initiated at Vanderbilt University. Participants will receive the REDCap links in their in email to complete the surveys online.Hospital utilizations: This will be measured at the end of the study by a review of the electronic medical records for emergency department or urgent care clinic visits and in-patient admissions.Quality of life: This will be measured longitudinally by the Functional Assessment of Cancer Therapy-General (FACT-G) questionnaire administered in-person at study entry, midpoint, and end of study [23]. Now in its fourth version, this questionnaire is well validated and has been translated into nearly 50 different languages and has been used extensively worldwide. It has four subscales: Physical Well-Being, Social/Family Well-Being, Emotional Well-Being, and Functional Well-Being.Cancer-related fatigue: This will be assessed by the Functional Assessment of Chronic Illness Therapy - Fatigue Version 4 (FACIT-F) at study entry, midpoint, and end of study [24]. It is a self-administered 13-item questionnaire validated for use in chronic illness and frequently used with cancer patients.Anxiety: The Generalized Anxiety Disorder 7-Item Scale (GAD-7) will be used to assess anxiety [25]. This self-administered 7-item questionnaire is a valid and efficient tool commonly used in both clinical practice and research studies to assess the severity of anxiety.Usability and Satisfaction: This is a study-specific questionnaire designed by the authors to collect usability and satisfaction information.

### Statistical Analysis Plan

#### Sample Size Estimation

A sample size of 82 subjects, 41 in each arm (control vs intervention) is sufficient to detect a 10-point difference in mean medication adherence rates (measured by MEMS) between the two groups, assuming equal standard deviation of 16 using a two-tailed *t* test of difference between means with 80% power and a 2-sided alpha of .05. Considering a dropout rate of 20%, the sample size required is 104 (52 subjects per group). Medication adherence rates in the literature vary based on the methods of measurement. The assumptions used in our sample size calculations are based on similar studies, especially those that used the MEMs device as the primary measure of medication adherence [4,6]. A total of 52 participants will be randomly assigned to receive the mobile intervention and will also continue to receive the standard of care for OAMs at the DFCI (intervention group), while the remaining 52 participants will be assigned to the control group that will continue to receive the standard of care at DFCI (usual care group). Participants will be followed up for a total of 3 months.

#### Statistical Analysis

Data analyses will be done with data analysis and statistical software STATA, version 13, with an alpha of .05 set a priori. Although there are multiple assessment points, all subjects will be followed up for a total of 12 weeks in this 2-parallel group study design. The intention-to-treat approach will be used for all analysis. Descriptive statistics, means (normally distributed) and medians (skewed) continuous data and percentages for categorical variables, will be used to summarize baseline demographic and technology use characteristics by study arm. We will examine for group differences in the primary outcome, percentage of pills taken, by *t* tests or by the non-parametric Mann-Whitney tests if the data are not normally distributed. Logistic regression will be used to identify potential predictors of adherence. For secondary outcomes, continuous outcomes will be analyzed using *t* test or Mann-Whitney test, and categorical variables will be compared using chi-square tests. Given the longitudinal mode of data collection, a repeated measure analysis of variance will be used to evaluate changes from baseline.

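### For the four repeated symptom and quality-of-life scales, the stated t test and repeated-measures ANOVA should give way to one baseline-adjusted mixed model with a single named test

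*Protocol article*

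**What the plan says.** All references are to the protocol article.

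- **Tests for secondary outcomes (Statistical Analysis).** The sentence beginning "For secondary outcomes, continuous outcomes will be analyzed using" names a t test or Mann-Whitney test, with chi-square tests for categorical variables. No baseline term is mentioned, and the text does not say whether final scores or change scores are compared.
- **Longitudinal analysis (same section).** The next sentence reads: "Given the longitudinal mode of data collection, a repeated measure analysis of variance will be used to evaluate changes from baseline". Neither analysis is named as the deciding one.
- **Analysis set (same section).** "The intention-to-treat approach will be used for all analysis".
- **Measurement times (Secondary Outcomes; Abstract, Methods).** FACT-G and FACIT-F are measured at entry, midpoint and end. MDASI has those three visits, and in addition "we will also assess symptoms in between study visits at weeks 3 and 9", which makes five. For anxiety (GAD-7) the Abstract gives start, midpoint and endpoint.
- **Dropout (Sample Size Estimation).** "Considering a dropout rate of 20%, the sample size required is 104 (52 subjects per group").

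**The concern.** Each of the four scales has a baseline score and at least two later scores. The natural question is how far the arms differ at 12 weeks, given where patients started. The stated methods answer it poorly in three ways.

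1. **Precision.** A t test on final scores makes no use of the baseline. A contrast of change scores uses it, but with a fixed slope of one, which is less efficient than letting the data set the slope.
2. **Missed visits.** Repeated-measures ANOVA in its classical form needs every visit from every patient. A long-format version can keep partial records, but it then leans on sphericity and on an approximate error term for unbalanced data. Neither sits well with a trial that plans for one patient in five to drop out and promises intention-to-treat throughout. The two extra MDASI assessments, added to catch short-lived symptoms, would give more occasions to lose a patient from the MDASI analysis.
3. **Two analyses.** Read literally, each scale gets a two-group test and an ANOVA. If they disagree, the text does not say which one counts.

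At stake are the precision and clarity of the secondary conclusions on symptoms, quality of life, fatigue and anxiety.

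**Working it through.** **Inputs from the article.** Difference 10 points; SD 16 ("assuming equal standard deviation of 16"); 80% power; two-sided alpha 0.05; 41 per arm evaluable; 52 per arm randomised; 20% dropout.

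**Assumed inputs, not in the article.** Correlation ρ between baseline and final score of 0.3 to 0.7, with equal variance at both times; 5% to 10% of remaining patients missing each interim visit. The 20% is stated for the primary-outcome sample size, so applying it to the questionnaires is an inference.

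**Step 1: the plan's own figure.** The article says "A sample size of 82 subjects, 41 in each arm (control vs intervention) is sufficient to detect a 10-point difference".

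- n per arm = 2 × (1.960 + 0.842)² × 16² / 10² = 40.2, rounded up to 41. Power at 41 is 80.8% by the normal approximation and 79.8% by the exact t test.
- 41 / 0.8 = 51.25, rounded up to 52 per arm, or 104.

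Both figures reproduce. This point does not touch the sample size.

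**Step 2: precision.** Variance of the arm difference relative to a final-score t test:

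- baseline adjustment: 1 − ρ²
- change score: 2(1 − ρ), which exceeds 1 when ρ < 0.5
- baseline adjustment relative to change score: (1 + ρ)/2, always below 1 for ρ < 1

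The detectable effect at 80% power with 41 per arm is (1.960 + 0.842) × √(2/41) = 0.62 SD for the final-score t test. The other methods multiply this by the square root of their variance ratio.

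| ρ | Variance ratio, adjusted | Variance ratio, change | Detectable, adjusted (SD) | Detectable, change (SD) | Power at 0.62 SD, adjusted | Power at 0.62 SD, change |
|---|---|---|---|---|---|---|
| 0.3 | 0.91 | 1.40 | 0.59 | 0.73 | 84% | 66% |
| 0.5 | 0.75 | 1.00 | 0.54 | 0.62 | 90% | 80% |
| 0.7 | 0.51 | 0.60 | 0.44 | 0.48 | 97.5% | 95% |

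In patients, adjustment is worth 41 / (1 − ρ²), or about 45, 55 and 80 per arm instead of 41.

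**Step 3: complete cases.** Patients reaching the end: 104 × 0.8 = 83.2. Patients with every visit: 83.2 × (1 − m)^k, with m the assumed miss rate and k the number of interim visits.

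- Three-visit scales (k = 1): 83.2 × 0.95 = 79.0; 83.2 × 0.90 = 74.9.
- MDASI (k = 3): 83.2 × 0.95³ = 71.3; 83.2 × 0.90³ = 60.7.

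Beyond dropout, the loss is about 4 to 8 patients on the three-visit scales and 12 to 23 on MDASI.

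**Step 4: does completer analysis bias the result?** An illustrative simulation used 52 per arm, three visits, ρ = 0.6, no true effect and dropout of about 20%.

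- Dropout driven by the midpoint score in one arm only: the completers' t test was off by 0.12 SD, with type I error 8.3%. An estimate that also used baseline and midpoint scores was off by 0.01 SD and had about 35% less variance.
- Same dropout mechanism in both arms: no bias in the completers' test (type I error 4.6%), only less precision.

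**The case against.** The strongest reply is that a journal article condenses the plan. Handling of missing data, error structure and the deciding time point are commonly left to the full document, and nowhere does the article state a complete-case analysis. The general test sentence may be meant mainly for outcomes without a baseline score (hospital utilisation, usability), with the ANOVA meant for the repeated scales. On that reading there are no competing tests. The gain may also be small: at ρ = 0.3 the detectable effect moves only from 0.62 to 0.59 SD, and the three-visit scales lose few patients. All of this concerns secondary outcomes with no stated power.

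Much of this stands, and it limits the size of the point. It does not remove it, because the criticism is of methods the article names. The test sentence is not restricted to outcomes without baseline. Even if it were, an ANOVA of change is still less efficient than baseline adjustment.

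A reader might infer more than the article supports:

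- *That the ANOVA wastes the baseline or dilutes the effect by averaging in the baseline visit.* The sentence concerns change from baseline, so baseline is used. Dilution would arise only from a group main effect with baseline as one of its levels, and the article names no such test.
- *That intention-to-treat is in fact broken.* This depends on how the ANOVA is run. A long-format version can keep partial records.
- *That dropouts will be the patients with the worst symptoms, so results will be biased.* Nothing in the article documents this, and Step 4 shows bias only when dropout differs between arms in its link to the score.

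**Conclusion.** The point holds as an inefficient and ambiguous choice of method for MDASI, FACT-G, FACIT-F and GAD-7. It is of moderate weight: it should be changed, but it threatens neither the primary analysis nor the sample size.

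The precision loss against baseline adjustment is certain in direction. Its size rests on the assumed correlation: 9% to 49% of the variance of a final-score t test over ρ = 0.3 to 0.7. The loss of patients applies to the classical ANOVA and rests on the assumed miss rates and on carrying the 20% dropout over to the questionnaires. Bias is possible but not shown.

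**What to change.** For each of the four scales, replace both stated analyses with one linear mixed model for repeated measures: post-baseline scores as response; arm, visit, arm-by-visit and baseline score as fixed effects; unstructured covariance. Name the arm difference at week 12 as the single test for each scale.

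Three details belong with it:

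- The model uses all available post-baseline data under missing at random. Patients with no post-baseline value still drop out of it, so add a sensitivity analysis for them, or place baseline in the response vector with the arm means constrained equal at entry.
- If scores are skewed, which is what the Mann-Whitney option was there for, use robust or bootstrap standard errors.
- Keep the t test, Mann-Whitney or chi-square test for hospital utilisation and usability, which have no baseline score.

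The cost is a change of wording and a little more analysis work. The stated software fits this model and no new data are needed. The price is reliance on the missing-at-random assumption, which should be stated.
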